**Drop-out and Termination criteria**
Patients are to be terminated on condition that they correspond with one of the following criteria:
◆ The participant withdraws from the trial (because the patient becomes invalid, lost, or dies accidently)
◆ The interviewee is terminated during the trial (for reasons such as poor compliance, withdrawal of informed consent, prohibition of drug use, or safety-related problems)
◆ When SAEs or other diseases occur, it is not appropriate to continue to conduct
◆ Incomplete data affects the evaluation of efficacy and safety
◆ A serious violation of trial procedures has occurred
◆A hepatocellular injury is detected because of the abnormally elevated liver enzymes: level of alanine transaminase (ALT) or aspartate transaminase (AST) is more than three times of the upper limit of normal (ULN)

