Currently, several treatment alternatives, including traditional Chinese medicine (TCM), which is a supplementary therapy for hyperuricemic nephropathy, are available. During the treatment with TCM, phlegm turbidity stasis resistance is considered to be the main pattern observed in stages 3–4 (advanced stage) CKD patients with hyperuricemic nephropathy based on syndrome differentiation. The Jiangniaosuan formulation (JNSF) contains seven herbs, i.e., 10 g Semen Vaccariae, 10 g Semen sinapis, 15 g Semen plantaginis, 10 g Dioscoreae hypoglaucae rhizoma, 10 g Fructus crataegi, 15 g Radix clematidis, and 10 g Radix et rhizoma rhei. JNSF is mainly used to dissolve phlegm and reduce turbidity, promote blood circulation, and promote collaterals, which is in accordance with the pattern observed in patients at advanced stages of hyperuricemic nephropathy.

Our previous work has demonstrated that JNSF can lessen urate crystallization, suppress renal inflammation and improve renal function in rats with hyperuricemic nephropathy, and the changes could be contributed to suppressing the TLR4/NF-κB signaling pathway [9]. However, no evidence-based clinical study has appraised the efficacy and safety of the clinical application of JNSF for the therapy of hyperuricemic nephropathy. Consequently, we conduct a randomized, double-blinded, placebo-controlled clinical approach to assess whether clinical efficacy could be improved with the use of JNSF for the treatment of stages 3–4 CKD patients with hyperuricemic nephropathy. This would also provide an effective approach and help us accumulate evidence-based medical support for the treatment of hyperuricemic nephropathy in stages 3–4 CKD patients using traditional Chinese medicine.

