### Measurement items and procedure

2.10

Several relevant examinations will be conducted before the baseline, at the baseline, at week 4, 12, and 24 during treatment. General information will be collected, including the name, age, sex, height, weight, contact information, physical examination, laboratory examination results, and history of present illness, other diseases, personal life, menstruation, marital and fertile, allergy, and family members.

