### Primary outcome

2.11

The primary outcome is the eGFR value, and it is calculated using the CKD-EPI creatinine equation, to evaluate the kidney function before and after the intervention on visit 1 to 4 (listed in Table 3).

**Table 3 tbl3:** The measurement items and study procedure.

Items	Screening	Treatment			
Timepoint	V0(-1 weeks)	V1(0 week)	V2(4 weeks)	V3(12 weeks)	V4(24 weeks)
Informed consent	X				
Inclusion/exclusion criteria	X				
Demographic data	X				
Medical history	Χ				
Drug combination	Χ	Χ	Χ	Χ	Χ
Randomization		Χ			
Allocation		Χ			
Physical examination	Χ	Χ	Χ	Χ	Χ
TCM symptoms	Χ	Χ	Χ	Χ	Χ
Kidney function (eGFR, Scr, BUN, SUA)	Χ	Χ	Χ	Χ	Χ
Serum electrolytes	Χ	Χ		Χ	Χ
24-h urine test	Χ	Χ		Χ	Χ
UACR	Χ	Χ		Χ	Χ
Renal tube function	Χ	Χ		Χ	Χ
Inflammatory mediators		Χ		Χ	Χ
Renal ultrasound	Χ	Χ			Χ
Blood, urine and stool routine	Χ	Χ		Χ	Χ
Hepatic function	Χ	Χ		Χ	Χ
Electrocardiogram	Χ	Χ		Χ	Χ
Adverse events			Χ	Χ	Χ
Drug distribution		Χ	Χ	Χ	
Drug collection			Χ	Χ	Χ

X indicates that data need to be collected during the visit.

TCM, traditional Chinese medicine; eGFR, estimated glomerular filtration rate; Scr, serum creatinine; BUN, blood urea nitrogen; SUA, serum uric acid; UACR, urine microalbumin to creatinine ratio.

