### Data and safety monitoring

2.14

The investigators will receive unified training and data monitoring committee (DMC) will be set up with experienced physicians and statisticians, who have no competing interests, to conduct monitoring once every three months for the entire research process. The trained investigators will fill out the case report form (CRF), and use EpiData 2.1a software to establish the special database system for this trial according to the items in the CRF. Two independent data administrators will type the data and conduct audits to ensure that the data in the database is consistent with the results in the CRF.

The participant will be monitored in the circumstance that an adverse event (AE) occurs, until their AE disappears. As patients diagnosed with Hyperuricemic Nephropathy frequently suffer from gout attacks, we will advise patients to oral intake anti-inflammatory drug or low-dose corticosteroids until the pain is relieved. AEs will be reported to the principal investigator to assess and the IRB. The investigator will conduct a follow-up interview and record the results supposing that the intervention induces the AE. Safety monitoring results will be reported to principal investigator weekly and the IRB.

The following are potential events related to the safety of the intervention.◆The eGFR is decreased by ≥ 50%◆The serum creatine levels is doubled than the previous blood test◆The patient is in the progression of CKD stage 5◆The patient occurs serious cardiovascular or cerebrovascular event◆The heart rate of patient is less than 40 bpm◆The patient occurs an unexpected event that is supposed to the intervention by the physicians

The following are potential SAEs.◆The patient occurs fatal or life-threatening complications◆The patient is dead or persistent and significant disabled◆The patient is hospitalized or receive large-scale medical intervention to prevent progression◆The patient develops any event that physicians diagnose to be significantly hazardous or harmful

The trial can be terminated for the following reasons.◆The number of enrolled patient is insufficient◆The allocation codes are unwrapped or the process of blinding has been nullified if the proportion of unsealed envelopes with emergency plans is more than 20% during the trial◆SAEs are supposed to associated with the intervention drug in the trial, which may signify that the safety of the drug has serious flaws

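### Table 1 stops treatment at ALT or AST above three times ULN, but Table 3 schedules no liver test between week 0 and week 12; the week-4 blood draw could carry one

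*Protocol article*

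**What the plan says.** The rule is in Table 1 of the protocol article, under the drop-out and termination criteria. The list opens with "Patients are to be terminated on condition that they correspond with one of the following criteria", and its last item is a liver injury shown by a "level of alanine transaminase (ALT) or aspartate transaminase (AST) is more than three times of the upper limit of normal (ULN".

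The timetable is in section 2.10 and Table 3. Section 2.10 states: "Several relevant examinations will be conducted before the baseline, at the baseline, at week 4, 12, and 24 during treatment". Table 3 then assigns tests to visits:

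- The row "Hepatic function" is marked at V0, V1 (week 0), V3 (week 12) and V4 (week 24). V2 (week 4) is blank.
- The row that begins "Kidney function (eGFR, Scr, BUN, SUA" is marked at all five visits, V2 included.
- The row "Drug distribution" is marked at V1, V2 and V3.
- Physical examination and concomitant drugs are marked at all five visits. Adverse events are marked at V2, V3 and V4.

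Two other places bear on the point. The Background says that "no evidence-based clinical study has appraised the efficacy and safety of the clinical application of JNSF" in this disease. Section 2.14 says: "Safety monitoring results will be reported to principal investigator weekly and the IRB".

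**The concern.** The stopping rule depends on a laboratory value. For a patient without symptoms it can act only when someone measures ALT and AST. After baseline that is scheduled twice, and the second time (week 24) is the end of treatment, so week 12 is the only scheduled test that can still change dosing.

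At week 4 the patient is examined, asked about adverse events, bled for kidney function and given eight more weeks of study drug, with no liver result since dosing began. A silent enzyme rise would not show in the examination or the adverse event record.

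What is at stake is patient safety. The herbal product has, by the protocol's own account, no evidence-based clinical safety data in this disease, and the protocol treats the liver as a risk: it excludes hepatic dysfunction, gives the liver its own stopping threshold and lists hepatic function among the monitored parameters in the Discussion. Power, type 1 error and the primary analysis are not involved.

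**Working it through.** The plan gives no figure of its own on this point, so the check is to read Table 3 by column and count intervals.

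**Inputs (Table 3; group sizes from section 2.5)**

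| Week | -1 | 0 | 4 | 12 | 24 |
|---|---|---|---|---|---|
| Liver tests | X | X | blank | X | X |
| Kidney function blood | X | X | X | X | X |
| Study drug handed out | | X | X | X | |

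The blank at week 4 is unlikely to be a reading fault. The rows for electrolytes, UACR and ECG show the same pattern, while kidney function is marked at week 4. No other section schedules a liver test between weeks 0 and 12.

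**Step 1. Gaps between scheduled liver tests on treatment**

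- Current (weeks 0, 12, 24): 12 and 12 weeks.
- With week 4 added (weeks 0, 4, 12, 24): 4, 8 and 12 weeks.

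The longest gap in weeks 0 to 12 falls from 12 to 8 weeks. The gap from week 12 to week 24 stays at 12 weeks.

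**Step 2. Wait from onset to the next scheduled test**

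Assumptions, not taken from the documents: a rise persists until it is tested, and onset is uniform over the period considered. The mean wait for onset within an interval is the time of the next test minus the midpoint of the interval.

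| Onset | Current | With week-4 test |
|---|---|---|
| Weeks 0-4 (midpoint 2) | 12 - 2 = 10 weeks | 4 - 2 = 2 weeks |
| Weeks 4-12 (midpoint 8) | 12 - 8 = 4 weeks | 12 - 8 = 4 weeks |
| Weeks 12-24 (midpoint 18) | 24 - 18 = 6 weeks | 24 - 18 = 6 weeks |

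Weighting by interval length:

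- Weeks 0-12, current: (4 x 10 + 8 x 4) / 12 = 72 / 12 = 6.0 weeks.
- Weeks 0-12, with week 4: (4 x 2 + 8 x 4) / 12 = 40 / 12 = 3.3 weeks.
- Weeks 0-24, current: (72 + 12 x 6) / 24 = 144 / 24 = 6.0 weeks.
- Weeks 0-24, with week 4: (40 + 12 x 6) / 24 = 112 / 24 = 4.7 weeks.

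All of the gain comes from onset in weeks 0-4. A rise already present at week 4 is tested 12 - 4 = 8 weeks sooner.

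**Step 3. Extra assays**

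One per patient: 2 x 59 = 118 at most, fewer if some patients leave before week 4.

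**The case against.** The strongest reply is that nothing here is an error. The protocol has a numerical stopping rule, two liver tests before dosing, one in mid-treatment and one at the end, and a wish for one more is a matter of preference. Several supporting points are fair and stand:

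- The documents give no liver event rate or onset time and do not say that the product harms the liver. Week 4 is proposed because blood is already drawn then, not because risk is known to peak then.
- The gain is confined to onset in weeks 0-4, one sixth of treatment. Over 24 weeks the mean wait falls only to 4.7 weeks, and a 12-week gap remains at the end.
- A week-4 test comes before the possible febuxostat increase at week 5, so it cannot detect an effect of that increase. Drug for weeks 4 to 12 would probably be dispensed before the result is known.
- Other safeguards exist: chronic hepatitis and hepatic dysfunction are excluded, patients can be withdrawn for safety reasons, safety results are reported weekly, a monitoring committee reviews every three months, and unscheduled tests are not ruled out.
- Week 4 looks like a deliberately light visit, since many other tests are also blank there.
- The Background speaks only of a lack of evidence-based clinical study, and the Discussion refers to the investigators' own clinical observations, so some clinical use exists.

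These points limit the size of the concern but do not remove it. None identifies another scheduled liver test before week 12. None of the safeguards would reliably find a symptomless rise, because weekly reports and committee reviews can act only on values that have been measured. Nor is there an evident reason to leave the assay off a sample already being taken.

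**Conclusion.** The point holds as an inexpensive safety improvement the sponsor should make, not as a contradiction or a statistical error. The protocol sets a liver stopping threshold but schedules no test that could apply it in the first 12 of 24 weeks, while taking blood and dispensing drug at week 4.

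The reduction in gaps follows directly from Table 3. The mean waits also rest on uniform onset and persistence until tested. Depending on when the rise begins, the benefit runs from none (onset after week 4) to a mean of 8 weeks (onset in weeks 0-4). How many patients would benefit cannot be estimated from the documents.

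**What to change.** Mark hepatic function (ALT and AST) at V2 in Table 3, run on the blood already drawn for kidney function. State that the result is reviewed promptly after the week-4 dispensing, for example through the existing weekly safety report to the principal investigator, so that the Table 1 rule can be applied before week 12.

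The cost is the laboratory charge for at most 118 assays. The documents give no price, so calling this inexpensive is a judgement, but it needs no extra visit or blood draw and leaves the sample size and primary analysis unchanged. The week 12 to 24 interval is not shortened by this change.

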### Manufacture of study supplements

2.9

Patients will be randomized into either the JNSF or the control group and orally administered JNSF or placebo. Patients in the JNSF group will receive 10.2 g of the allocated intervention drug JNSF granules twice a day as oral administration, 30 min later than breakfast and dinner lasting 24 weeks. Respectively, the control group will accept 10.2 g of the placebo twice a day as oral administration. The appearance of the placebo is consistent with that of JNSF granules, in terms of packaging, appearance, particle shape, color and taste, but it contains one-tenth of the volume of drugs in the JNSF granules. The JNSF granules, as well as the placebo granules will be produced by Jiangyin Tianjiang Pharmaceutical Co., Ltd. (Wuxi City, Jiangsu Province, China), in accordance with certain manufacturing practices. The composition and function of each herb of JNSF have been outlined in Table 2.

**Table 2 tbl2:** Composition, effects and pharmaceutical action of the Chinese herbal medicines that constitute JNSF.

Ingredient	Granule dose	Effect (TCM)	Pharmaceutical action
Semen Vaccariae (wangbuliuxing)	10g	Promotes blood circulation and removes obstruction in collaterals	Attenuates human endothelial cell oxidative stress injury
		Promotes lactation for resolving carbuncle	Inhibits the growth and metastasis of malignant cells
Semen sinapis (baijiezi)	10g	Dissipates phlegm and expels retained fluid	Suppresses the mRNA expression of a panel of inflammatory mediators
		Resolves masses and removes edema	
Semen Plantaginis (cheqianzi)	15g	Reduces heat and induces diuresis	Reduces the content of urinary protein and UA and deregulates the expression of inflammatory mediators
		Eliminates dampness and frees strangury	
Rhizoma Dioscoreae hypoglaucae (fenbixie)	10g	Promotes diuresis and removes turbidity	Prevents oxidative stress and reduces levels of advanced glycosylation end products in the kidney
		Dispels pathogenic wind and dredges channel blockade	
Fructus crataegi (shanzha)	10g	Resolves food stagnation and invigorates the stomach	Improves lipid metabolism in the serum, liver, and adipose tissue
		Activates qi for resolving blood stasis	
Radix clematidis (weilingxian)	15g	Dispels pathogenic wind and eliminates dampness	Inhibits iNOS gene expression
		Removes obstruction in collaterals for relieving pain	
Radix et rhizoma rhei (dahuang)	10g	Removes heat and dredges the intestine	Anti-renal fibrosis
		Cools the blood and removes toxicity	
		Eliminates blood stasis for dredging channels	Increases the level of serum HIF-1α

iNOS, inducible nitric oxide synthase; HIF-1α, hypoxia inducible factor-1.

Each group will be provided with diet instructions [11], behavioral guidance and health-related education [12]. In addition, they will receive febuxostat as a urate-lowering therapy. The dose of febuxostat should be 20 mg once a day after study initiation to week 4, and this should be increased to 40 mg once a day at week 5 if the target is not met, and maintained until week 24.

Based on KDIGO Clinical Practice Guideline for CKD, medical decisions will be arranged reasonably for patients in either group as basic treatment on how to treat hypertension [13], renal anemia [14], CKD-MBD [15], lipid management [16], concurrent infections, as well as other diseases, with the exception of the TCM herb decoction. The investigators will record the name and dosage of any administered medicine.

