### Trial design

2.1

This study will be a prospective, single-centre, double-blinded, randomized, placebo-controlled trial involving stages 3–4 CKD patients with hyperuricemic nephropathy from mainland China. Patients are to be randomized into either the Jiangniaosuan formulation (JNSF) and febuxostat group or the JNSF placebo and febuxostat group. The intervention will be carried on for 24 weeks. This is designed as a superiority trial with allocation ratio = 1/1. The design of this study is laid out in Fig. 1.

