### Sample size

2.5

The sample size is issued from the primary outcome that is an alteration in baseline estimated glomerular filtration rate (eGFR). According to a previous report [8], the average eGFR value of the control group is estimated to be 34.7 mL/min/1.73 m^2^. After treatment with JNSF, the value for the intervention group could be increased by 10 mL/min/1.73 m^2^, and its standard deviation would be approximately 18.1 mL/min/1.73 m^2^. If we set the type 1 risk level at 5% and the power at 80%, we calculated that the minimum sample size for each group is 53 participants, using the formula: $t=\frac{\bar{x_{1}}-\bar{x_{2}}}{\sqrt{\frac{\left(n_{1}-1\right)s_{1}^{2}+\left(n_{2}-1\right)s_{2}^{2}}{n_{1}+n_{2}-2}\left(\frac{1}{n_{1}}+\frac{1}{n_{2}}\right)}}$. Assuming a drop-out rate of approximately 10%, we determined that the sample size should be increased to 59 in both groups, to include a total of 118 patients.

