Certain shortcomings are associated with this study. Firstly, the placebo contains excipients such as maltodextrin, caramel pigment, lemon yellow pigment, sunset yellow pigment, and a bittering agent. Theoretically, the use of placebos does not result in therapeutic effects in patients with hyperuricemic nephropathy. However, if these excipients demonstrate a therapeutic effect on patients with hyperuricemic nephropathy, this data has not been recorded. Secondly, in this trial, the age limits are set at 18–75 years, because of the following reasons: older people have multifarious concomitant diseases that increase the difficulty and risk of detection. Besides, we have taken the issue of patient compliance into consideration on the grounds that participants in this trial are mostly outpatients. The onset of hyperuricemic nephropathy with decreased kidney function occurs mostly in adults. Considering our limitations, we narrow down the age range to 18–75 years.

In summary, there are insufficient clinical researches available on systems of the combination of modern medicine and TCM to assess the efficacy and safety to treat patients with hyperuricemic nephropathy. This study will be a combination of an evaluation system for TCM and modern pharmacological researches, and its findings shall serve as a basis for future research in this field. The most prominent feature of this study is to understand TCM classification systems and TCM treatment characteristics based on syndrome differentiation in a more effective manner through the medium of EBM.

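### The control granule is said to hold one-tenth of the JNSF drug content, yet the Discussion reasons as if it held only excipients, so the comparator is not fixed

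*Protocol article*

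**What the plan says.** Section 2.1 declares a "prospective, single-centre, double-blinded, randomized, placebo-controlled trial" and adds: "This is designed as a superiority trial with allocation ratio = 1/1". The Abstract and section 2.7 (Blinding) also call the control a placebo.

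Section 2.9 (Manufacture of study supplements) says that "the control group will accept 10.2 g of the placebo twice a day as oral administration". It describes the placebo as matching JNSF in packaging, appearance, particle shape, color and taste, and then qualifies this: "but it contains one-tenth of the volume of drugs in the JNSF granules".

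The Discussion, in its paragraph on shortcomings, says that "the placebo contains excipients such as maltodextrin, caramel pigment, lemon yellow pigment, sunset yellow pigment, and a bittering agent". It continues: "Theoretically, the use of placebos does not result in therapeutic effects in patients with hyperuricemic nephropathy". The only reservation concerns the excipients: "if these excipients demonstrate a therapeutic effect on patients with hyperuricemic nephropathy, this data has not been recorded".

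Section 2.5 (Sample size) takes a control mean eGFR of 34.7 mL/min/1.73 m², a value for the intervention group that is higher by 10, and a standard deviation of 18.1. It does not mention what the control granule contains.

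**The concern.** The comparator defines the question. Read at face value, section 2.9 puts study drug in both arms for 24 weeks. The trial would then estimate the effect of full against one-tenth JNSF content. Read at face value, the Discussion says the control arm receives nothing with an expected effect, and the trial estimates the effect of adding JNSF to febuxostat. A result reported as placebo-controlled means something different in each case.

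If the control granule does contain JNSF and that content has any activity, two things follow. The efficacy difference would shrink toward zero, with a loss of power. Any harm that also occurs at the lower content would appear in both arms and be partly hidden in the comparison, although safety is a stated aim of the trial. The article does not say which situation applies.

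**Working it through.** **1. The two descriptions side by side.**

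| Point | Section 2.9 | Discussion |
|---|---|---|
| Content of control granule | one-tenth of the volume of drugs in JNSF | maltodextrin, three pigments, a bittering agent (open list) |
| Expected effect | not stated | none, theoretically |
| Possible source of an effect | not stated | excipients only |

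The first row is not a strict contradiction: a granule could hold some herbal content and be made up with excipients. The conflict lies in the other two rows. A paragraph on the limits of the placebo that weighs whether colorants and maltodextrin might act, and is silent on herbal content, does not describe a granule with one-tenth of the study drug. Nothing elsewhere in the article reconciles the two.

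**2. The wording of the fraction.** A volume of drugs is not defined. It could refer to granule mass, to the amounts of the seven herbs in Table 2 (10 + 10 + 15 + 10 + 10 + 15 + 10 = 80 g, one-tenth being 8 g), or to something else. The article does not say.

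**3. The plan's sample size, reproduced.** Inputs from section 2.5: difference 10, SD 18.1, type 1 error 5% (two-sided reproduces the figure), power 80%, drop-out 10%.

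- Normal approximation: n = 2 × (1.960 + 0.842)² × 18.1² / 10² = 51.4, so 52 per group.
- With the t distribution: 52.4, so 53 per group, as stated.
- Drop-out: 53 / 0.9 = 58.9, so 59 per group and 118 in total, as stated.

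The arithmetic is not in question.

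**4. Illustration of what an active control could cost.** Assume that the 10 units are the effect of JNSF against an inert control, and that the control granule keeps a fraction f of it. The contrast is then 10 × (1 − f). Power comes from the noncentral t with noncentrality contrast / (18.1 × √(2/53)) and 104 degrees of freedom. For f = 0.10 the contrast is 9.0 and the noncentrality is 9.0 / 3.516 = 2.56.

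| f (assumed) | Contrast | Power at 53 per group | n per group for 80% | Total with 10% drop-out |
|---|---|---|---|---|
| 0 | 10.0 | 80.4% | 53 | 118 |
| 0.05 | 9.5 | 76.3% | 58 | 130 |
| 0.10 | 9.0 | 71.8% | 65 | 146 |
| 0.20 | 8.0 | 61.6% | 82 | 184 |

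The row f = 0.10 is the case in which one-tenth of the drug gives one-tenth of the effect. No value of f can be taken from the documents.

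**The case against.** **The lists are compatible.** The Discussion introduces the excipients as examples, so one-tenth herbal content with added maltodextrin, pigments and a bittering agent fits both places. This stands as far as the lists go. It does not rescue the statement of no therapeutic effect, or the restriction of any possible effect to the excipients.

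**A low-content control may be deliberate.** The phrase sits in a sentence on matching appearance and taste, so it may serve the blinding. If the control were active in the same direction, the contrast would shrink; that costs power and does not inflate false claims of superiority. A positive result would remain valid for the comparison actually made. This stands as well, and it is why the point concerns the description of the control and not the choice of one.

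**Stronger readings.** A reader might infer that the control arm definitely receives low-dose JNSF and that the trial is not placebo-controlled. The documents do not settle this: the one-tenth wording is ambiguous and the Discussion points the other way. A reader might also infer that the sample size is wrong. Section 2.5 already writes the 10 units as the difference between the groups; that they are an effect against an inert control, to be reduced again for control content, is an inference. Steeper assumed dose-response curves would give much larger power losses than those shown, but the documents support no particular curve. Finally, nothing in the article reports control-arm adverse events as placebo rates, and the wording of the registration and the patient information is not shown, so no error can be alleged there.

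**Conclusion.** Wrong as written. Section 2.9 and the Discussion cannot both be left standing, because the Discussion's reasoning excludes herbal content that section 2.9 states. The comparator, and with it the meaning of any efficacy or safety result, is therefore not fixed. This conclusion rests on the text alone and on no assumption about dose-response.

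The effect on power is conditional. It arises only if the control contains active JNSF and if the assumed 10 units refer to an inert control. In the linear case, power would be about 72% instead of 80%. Which composition is correct cannot be decided from the documents.

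**What to change.** Check section 2.9 and the Discussion against the manufacturer's specification, and state one composition throughout the protocol, without prejudging which is right.

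- **If the control contains JNSF:** say so wherever the protocol now says placebo; define the efficacy and safety comparison as full versus one-tenth content; state what the one-tenth is a fraction of; correct the no-effect statement in the Discussion; and state in section 2.5 whether the 10 mL/min/1.73 m² difference refers to that contrast. If it does not, restate the power.
- **If it contains only excipients:** delete the one-tenth statement from section 2.9.

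The second case costs one sentence. The first is mainly a correction of the text. If the restated power falls short, the sponsor must either accept and report the lower figure or enlarge the trial; in the linear illustration, holding 80% would take 146 patients instead of 118.
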